## Abstract

**Introduction:**

Patients with congenital heart disease often need repeated operations throughout life to replace the pulmonary valve. Valve replacement with ‘injectable’ self-expanding valves (which is performed ‘off pump’ without the use of cardiopulmonary bypass, CPB) may result in quicker recovery and lower risk of major complications than valve replacement with conventional valves (which is performed ‘on pump’ with the use of CPB).

**Methods and analysis:**

We are conducting a multicentre, single-blind randomised controlled trial in patients with congenital heart disease and aged between 12 and 80 years. We will randomise participants in a 1:1 ratio to receive either ‘off pump’ injectable pulmonary valve replacement or ‘on pump’ conventional pulmonary valve replacement. The primary outcome will be the difference between the groups with respect to post-surgery blood loss (as measured by chest drain volume) in the first 24 hours. Secondary outcomes will include in-hospital outcomes (intensive care unit stay, inotropic/vasodilator support, chest drain volume in the first 12 hours post-surgery, time of readiness for extubation, blood products used in the first 24 hours post-surgery, time of fitness for discharge, valve and heart function 6 months post-surgery (assessed using cardiovascular magnetic resonance and ECHOCARDIOGRAPHY) and health-related quality of life 6 weeks and 6 months post-surgery.

**Ethics and dissemination:**

This trial has been approved by the South West Exeter Research Ethics Committee. Findings will be shared with participating hospitals and disseminated to the academic community through peer reviewed publications and presentation at national and international meetings. Patients will be informed of the results through patient organisations and newsletters to participants.

**Trial registration number:**

ISRCTN23538073

Strengths and limitations of this studyThis trial is the first randomised controlled trial (RCT) to assess the effectiveness of injectable tissue valves versus conventional tissue valves for pulmonary valve replacement (PVR).This is a multicentre RCT, with computer-generated concealed randomisation and participant blinding to minimise bias.We are including both children and adults (age range 12–80 years) to ensure the findings will be generalisable to a wide group of patients who need PVR.Although clinicians cannot be blinded to the patient’s treatment allocation, we will minimise bias by pre-defining all procedures for data collection and applying these to all participants in the same way.The primary and many of the secondary endpoints are clinical outcomes, based on objective criteria, which are important to patients, clinical teams and the NHS.

## Introduction

### Background and objectives

Most children born with complex congenital heart disease now reach adulthood. Post-surgery mortality following surgical correction, of tetralogy of Fallot, for example, has fallen from 5.5% in 1980^1^ to 0% in 2016.^2^ However, as long-term survival has improved late sequelae have become evident. Many of the patients operated on for tetralogy of Fallot and other forms of pulmonary valve disease require multiple operations throughout life to repair or replace poorly functioning pulmonary valves.

The standard operation for pulmonary valve replacement (PVR) involves opening the chest, exposing the heart and using cardiopulmonary bypass (CPB), (‘on pump’). CPB is a technique that temporarily takes over the function of the heart and lungs (pumping blood and oxygen through the body) and occasionally involves stopping the heart during surgery. CPB is associated with complications such as excessive bleeding and reperfusion injury in cases where the heart has to be stopped (damage to heart tissue occurs when the blood supply returns to the heart).

Injectable tissue valves (BioPulmonic, Biointegral Surgical) have been developed to replace conventional tissue valves for PVR. Injectable tissue valves can be implanted without the use of CPB (ie, ‘off pump’) and with less dissection of the heart. Case reports and small case series (<12 patients)^3–10^ have shown that injectable tissue valves are easy to implant and have satisfactory function. Pilot data have shown shorter operating time (2 hours less) and less blood loss (over 400 mL less) and blood product requirement (3 units less) in 6 ‘off-pump’ injectable pulmonary valve replacement (IPVR) patients compared with 7 ‘on pump’ PVR patients. No patient had a paravalvular leak (leak around the replaced valve) or more than mild pulmonary regurgitation at early follow-up, suggesting that IPVR is a safe procedure.^11^ There are no randomised controlled trials (RCTs) that have evaluated IPVR versus PVR.

We are conducting an RCT to determine whether IPVR leads to less blood loss, faster recovery, lower risk of post-surgery complications and good valve function in patients who need an operation to replace their pulmonary valve. We could not consider percutaneous transcatheter pulmonary valve replacement (TPVR), which is performed via cardiac catheterisation and therefore does not require open-heart surgery, because current TPVR valve sizes are only suitable for patients with a right ventricular outflow tract (RVOT) diameter of ≤27 mm which would exclude >80% of our eligible population.^12 13^ Further, all eligible patients will have native outflow tracts that are too distensile for robust fixation of a percutaneous valve.

## Aims and objectives

The main aim of the InVITe trial is to compare IPVR versus PVR in patients who need PVR. The objective is to estimate the difference between the groups with respect to:Post-surgery blood loss (as measured by chest drain volume) in the first 24 hours (primary outcome);A range of clinical post-surgery outcomes (intensive care unit (ICU) stay, inotropic/vasodilator support, chest drain volume in the first 12 hours, time until ready for extubation, blood products used in the first 24 hours, fitness for discharge (FFD) and valve-related complications during follow-up);Heart and valve function assessed using cardiovascular magnetic resonance (CMR) and Echocardiography;Health related quality of life (HRQoL).

## Methods

### Trial design and population

The InVITe trial is an early phase, multicentre, RCT comparing IPVR with PVR. We will recruit patients being referred for PVR at University Hospitals Bristol NHS Foundation Trust and University Hospitals Southampton NHS Foundation Trust.

### Eligibility criteria

Potential participants will be eligible if they are:Aged between 12 and 80 years.Have a valve size between 25–31 mm.Undergoing any of the following as either a first or a redo procedure:Replacement of the pulmonary valve;Replacement of the pulmonary valve with atrial septal defect which is amenable to closure via cardiac catheter or;Replacement of the pulmonary valve with right ventricular outflow tract (RVOT) reconstruction that does not require CPB if using an injectable valve.

Potential patients will be ineligible if they are:Prisoners or adults lacking capacity to consent.Aged between 12 and 15 years and under the care of social services.Undergoing an additional procedure that requires the use of CPB (eg, pulmonary valve or artery stenosis requiring patch reconstruction, intra-cardiac shunt, RVOT reconstruction requiring CPB, other anatomical heart corrections).Diagnosed with active endocarditis.Unwilling to undergo surgery involving a porcine product.Unable to assent/consent.

### Patient approach and consent

We will identify potential participants from clinic lists (elective patients) and theatre schedules (urgent patients) and they will be given an invitation letter and patient information leaflet (PIL) suitable to their age group. Parent(s)/guardian(s) of potential participants 12–15 years old will be given an invitation letter and parent/guardian information leaflet (P/GIL). Most patients and parent(s)/guardian(s) will have at least 24 hours to consider whether they would like to participate, although in some cases this time interval may be shorter; for example, patients admitted from other hospitals without prior notification to the research team. Written informed consent/assent will be obtained from the patients and/or their parent(s)/guardian(s) (where appropriate) prior to inclusion in the trial. Figure 1 shows the patient pathway.

**Figure 1 F1:**
[figure not shown]
Trial schema showing the recruitment pathway with the number of patients to be recruited, anticipated eligibility and recruitment rates.

### Trial interventions

For both operations the heart will be exposed through a standard incision for a heart operation (median sternotomy).

For IPVR operations a self-expanding no-react injectable BioPulmonic valve (Biointegral Surgical) will be used. The main pulmonary artery and the front of the heart will be dissected out. A purse-string stitch will be placed in the front of the heart and the size of valve required will be confirmed using an echocardiogram. If the main pulmonary artery is too big, it will be made smaller using a stitch to narrow it down. The valve injector will be inserted into the heart through the purse string and the valve will be deployed and sewn into position using 3 fixation stitches. If the patient becomes unstable during the surgery, CPB will be instituted. The position and function of the valve will be confirmed using transoesophageal echocardiography. The operation will then be completed in the standard manner.

For PVR operations, the type of tissue valve used will be according to the usual practice at the participating site and may include stented tissue valves (in adults particularly) or homografts (in children particularly). The heart will be freed from the scar tissue and the patient put on CPB. The pulmonary artery will be opened and the old valve removed. A new valve of the correct size will be sewn into place. In some cases the heart may need to be stopped for a short period of time. A patch may also be necessary to close the heart over the new valve. Once this has been completed and the heart has recovered from the effects of cardioplegic arrest, CPB will be discontinued and the operation will be completed in the standard manner.

All other aspects of participant’s care will be performed according to standard practice.

Participants will be followed up at 6 weeks (questionnaire completion) and 6 months (questionnaire completion, Echocardiography and CMR) post-surgery. The 6-month Echocardiography and CMR will coincide with routine hospital follow-up; so we expect minimal loss to follow-up. A 6-month follow-up period will provide adequate data to inform early recovery.

### Randomisation

Trial allocations will be generated by a computer using block randomisation with varying block sizes. Participants will be randomly assigned in a 1:1 ratio and randomisation will be stratified by centre. If a participant’s operation is unexpectedly rescheduled, the trial number and randomised allocation will be retained.

### Trial outcomes

The primary outcome will be post-surgery blood loss as measured by the chest drainage volume in the first 24 post-surgical hours. The secondary outcomes include:Post-surgery time to ‘readiness for extubation’. The following criteria will be documented at the time of extubation (when all criteria should be met): normal temperature, cardiovascular system stable, no metabolic imbalance, blood loss decreasing and below a defined rate, able to clear respiratory secretions, patient awake, no residual muscle paralysis and adequate analgesia;Length of ICU stay;Inotropic/vasodilator support;Chest drain volume in the first 12 post-surgical hours;Blood products used in the first 24 post-surgical hours (red blood cells, fresh frozen plasma, platelets, human albumin solution, cryoprecipitate) and bleeding events that may or may not lead to re-operation;Post-surgery time to FFD, defined as when all of the following criteria are met: normal temperature, pulse and respiration, normal oxygen saturation on air, normal bowel function, physically mobile;CMR assessment of valve and heart function at 6 months, defined as presence and degree of pulmonary regurgitation, end-diastolic volume and right ventricular ejection fraction;Echocardiographic assessment of valve function at routine follow-up at 6 months, defined as presence and degree of pulmonary regurgitation and residual valve stenosis, measured as peak velocity through the valve;HRQoL at 6 weeks and 6 months post-surgery (EuroQol EQ-5D in patients ≥18 years and EQ-5D-Y in patients <18 years, SF36 in patients ≥18 years and child health questionnaire in patients <18 years);Valve-related complications up to 6 months post-surgery.

### Data collection

The schedule of data collection is shown in table 1. Data will be collected from medical notes and hospital records, entered onto a bespoke database and stored on a secure server. Access to the database will be limited to authorised personnel. Data will be collected and retained in accordance with the UK Data Protection Act 2018.

**Table 1 T1:** Schedule of data collection

Data item	Pre-surgery	During surgery	Post-surgery (up to and including discharge)	6 weeks post-surgery	6 months post-surgery
Screening and consent data	*✓*				
Baseline data (patient demographics, medical history, medications)	*✓*				
Cardiovascular magnetic resonance imaging	*✓*				*✓*
Echocardiography	*✓*				*✓*
Randomisation allocation	*✓*				
Intervention (injectable pulmonary valve replacement /PVR)		*✓*			
Inotropic/vasodilator support			*✓*		
Chest drain volume in the first 12 and 24 hours			*✓*		
Blood products used in the first 24 hours			*✓*		
Readiness for extubation			*✓*		
Intensive care unit stay			*✓*		
Fitness for discharge			*✓*		
Health related quality of life				*✓*	*✓*
Follow-up questionnaires to collect all serious post-surgery complications and safety data				*✓*	*✓*

### Blinding

We will blind participants to their treatment allocation and assess the efficacy of blinding at 6 weeks and 6 months post-surgery via questionnaires. We will record any instances of unblinding. Staff responsible for the care of the patient will be aware that the patient is blinded and asked not to disclose the patient’s treatment allocation. It will not be possible to blind surgeons, staff responsible for the care of the patient or research nurses to the participant’s treatment allocation. Details of the procedure are needed to order an injectable valve of the required size and also need to be recorded in the medical notes.

### Sample size calculation

A sample size of 60 (30 per group) will have 80% power to detect an approximate 50% reduction in chest drainage volume (effect size on logarithmic scale of −0.73) over the first 24 hours at a 5% significance level (two-tailed). This target difference is large but is entirely consistent with the >70% reduction observed in a small non-randomised comparison of patients who had IPVR and PVR.^11^

### Statistical analysis

The trial will be analysed on an intention-to-treat basis, that is, outcomes will be analysed according to the treatment allocation. Any non-adherence to the allocated group will be documented. The primary outcome (chest drainage volume in the first 24 post-surgical hours) will be analysed using linear regression (on the logarithmically transformed values as the distribution is expected to be skewed). All secondary outcomes will yield either binary, quantitative, time-to-event or longitudinal data, and will be analysed using logistic regression (binary outcomes), linear regression (quantitative outcomes), survival methods (time-to-event outcomes). Outcomes with repeated measures (longitudinal data) will be analysed using mixed models which allow for unbalanced data. Alternative correlation structures will be considered and the sensitivity of the results to the choice of the structure examined. Analyses will be adjusted for the centre (stratification factor). Outcomes will be reported as effect sizes with 95% CIs.

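### The primary model for 24-hour drain volume adjusts for centre only; adding body size and previous cardiac surgery would recover precision in a design with no power to spare

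*Protocol article*

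**What the plan says.** All references are to the protocol article.

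- **Outcome (Trial outcomes):** "The primary outcome will be post-surgery blood loss as measured by the chest drainage volume in the first 24 post-surgical hours". No indexing to weight or body surface area is mentioned.
- **Model (Statistical analysis):** "The primary outcome (chest drainage volume in the first 24 post-surgical hours) will be analysed using linear regression", fitted "on the logarithmically transformed values as the distribution is expected to be skewed".
- **Adjustment (Statistical analysis):** "Analyses will be adjusted for the centre (stratification factor". No other covariate is named.
- **Randomisation:** "Participants will be randomly assigned in a 1:1 ratio and randomisation will be stratified by centre". No other stratification factor is named.
- **Population (Eligibility criteria):** ages 12 to 80 years, a valve size of 25–31 mm, and the listed pulmonary valve replacements "as either a first or a redo procedure".
- **Baseline data (Data collection, Table 1):** "Baseline data (patient demographics, medical history, medications" are collected before surgery.
- **Sample size calculation:** 60 patients (30 per group), 80% power, two-sided 5%, effect of −0.73 on the log scale, described as roughly a halving.
- **Risk of bias:** a detailed analysis plan will be written before the database closes and groups are compared. It is not shown.

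**The concern.** Absolute drain volume plausibly rises with body size and with the amount of scar that has to be dissected. The eligible population can vary on both. Taking logs deals with skew and turns a proportional size effect into an additive one, but does not remove it. It stays in the residual unless size is in the model.

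What is at stake is precision. A larger residual variance means a wider confidence interval and lower power for the single primary comparison. Adjustment is attractive here because, in a linear model on log volume, adding baseline covariates leaves the treatment parameter with the same meaning, a ratio of volumes. It also recovers information without recruiting anyone. The section on recruitment issues reports 17 consented and 13 operated so far, and says that recruitment is slower than anticipated.

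**Working it through.** **Step 1. Reproduce the stated sample size.** Inputs from the Sample size calculation: effect 0.73 on the log scale, two-sided 5%, 80% power. No SD is given.

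- exp(−0.73) = 0.48, a 52% reduction, which agrees with the stated approximate 50%.
- n per arm = 2 × (1.96 + 0.84)² × SD² / 0.73². With SD = 1 this is 29.5, rounded up to 30, which matches the plan. The implied log-scale SD is therefore about 1.
- Power with 30 per arm: 80.7% by normal approximation and 79.4% by the non-central t. A full 80% by t needs 31 per arm.

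The stated figure is sound, but there is no margin in it.

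**Step 2. Power after adding two covariates.** If body size and previous surgery explain a share R² of log-volume variance, the residual SD is √(1 − R²) and the standard error is √(1 − R²) × √(2/30). Power comes from the non-central t with 60 − 5 = 55 degrees of freedom. R² is an assumption.

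| R² (assumed) | Residual SD | Standard error | Power at 0.73 |
|---|---|---|---|
| 0 | 1.000 | 0.258 | 79.3% |
| 0.05 | 0.975 | 0.252 | 81.3% |
| 0.10 | 0.949 | 0.245 | 83.3% |
| 0.20 | 0.894 | 0.231 | 87.4% |

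The first row is the cost if the covariates are useless: about 0.1 percentage point against 79.4%.

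**Step 3. What R² is plausible?** The document gives nothing, so these are illustrations.

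- *Body size alone.* If volume is proportional to weight and total SD is 1, R² equals the squared SD of log weight. For an assumed SD of 0.20 to 0.35, R² is 0.04 to 0.12 and power is about 81% to 84%.
- *Body size plus previous surgery.* Assume a log-weight SD of 0.30 (R² 0.09), half the patients with previous surgery, independent of weight, and a 1.2- to 2.0-fold effect on drainage. The second term adds 0.25 × (ln 1.2)² = 0.008 to 0.25 × (ln 2.0)² = 0.120. Total R² is 0.098 to 0.210 and power is about 83% to 88%.

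**Step 4. Chance imbalance, as a picture of the same variation.** If half the patients have had previous surgery (assumed), the hypergeometric probability that the arms differ by 20 percentage points or more is about 20%. At an assumed 1.5-fold effect, a 20-point gap moves the estimated volume ratio by exp(0.20 × ln 1.5) − 1 = 8%. This sampling variation is already inside the centre-only standard error, so it must not be added to the power loss in Steps 2 and 3.

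**The case against.** The strongest reply is that nothing is stated wrongly. Adjusting for the stratification factor matches the design, the article does not say that other covariates are excluded, and a detailed analysis plan is promised. This stands in part. The unseen plan may add covariates. But the article does not leave the topic open: it names an adjustment, and that adjustment is centre.

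A second reply is that every driver of the gain is assumed. This stands. The 25–31 mm valve requirement may also narrow the range of body size more than the age limits suggest.

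A third reply is that first or redo status may not measure scar. This stands too. In the Eligibility criteria that phrase qualifies the valve replacement. The Introduction describes patients already operated on for tetralogy of Fallot, and Trial interventions treats freeing the heart from scar as an ordinary step of the conventional operation. A first valve replacement can therefore be a reoperation, so previous sternotomy or cardiac surgery fits the mechanism better.

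A reader might infer three stronger things that the document does not support:

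- *That the centre-only analysis is biased or inflates type I error.* Randomisation keeps it valid.
- *That chance imbalance is a separate harm on top of lost power.* It is the same variation, already reflected in the confidence interval.
- *That power could rise well above 90% by supposing a log-scale SD of 0.8 or 0.6 with an effect of 0.73 SD.* That changes the target to a 44% or 35% reduction (1 − exp(−0.73 × 0.8) and 1 − exp(−0.73 × 0.6)). With the plan's own −0.73 on the log scale, those SDs would already give 93.5% and 99.6% power unadjusted, leaving little to gain.

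**Conclusion.** The point holds as an efficiency weakness of moderate importance. It is neither an error in the sample size nor a threat to validity. At the implied log-scale SD of about 1, the planned model has 79.4% power by t. Adding body size and previous surgery would plausibly bring a few percentage points, within the range tabulated for R² 0.05 to 0.20. The result rests on an R² that the document does not supply, and the gain could be small if the valve-size limit makes patients similar in size or if nearly all have had previous surgery. The recommendation still holds because the trade is lopsided: a possible gain of several points against a loss of about 0.1 point.

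**What to change.** Before any comparison between groups, pre-specify the primary model as log(24 h drain volume) on allocation, centre, log body weight (or body surface area) and previous sternotomy or cardiac surgery (yes/no). If pooled baseline data, read without regard to allocation or outcome, show that previous surgery is near-universal, use first/redo status instead. Use the same covariates for the 12-hour volume, and report the centre-only model as a sensitivity analysis.

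The change costs wording in the protocol or analysis plan and two degrees of freedom. Demographics and medical history are already collected at baseline; if weight is not a database field, it is one value per patient from the chart. The sample size need not change.

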### Changes to the protocol since REC approval

We made three major changes to the protocol before recruitment began. First, we decided to blind participants to ensure validity of the patient-reported outcome data. Second, we decided that it was not feasible to blind the research nurses to the treatment allocation as they would be required to order the valves. Third, initially we intended to establish a Data Monitoring and Safety Committee to oversee the trial. Given that the trial has a relatively low target sample size, a short follow-up period and we expect very few serious adverse events, it is hard to conceive of an interim analysis (eg, after 50% of the participants have been recruited) with sufficient power to identify a safety issue that would require action to be taken. We concluded, therefore, that it was sufficient for the safety data to be reviewed by the Trial Management Group and Trial Steering Committee for Cardiovascular Studies, a sub-group of the University Hospitals Bristol NHS Foundation Trust Cardiovascular Research Board. Shortly after opening to recruitment, we made one major change to the protocol, to extend the baseline data collection to include the pre-surgery echocardiographic and CMR results. Finally, protocol and study documents have been amended to allow the central analysis of CMR data. Version 6.0 (dated 02/07/2018) of the protocol is currently in use. The relevant regulatory approvals will be obtained for amendments to the protocol and study information leaflets. Relevant parties (eg, investigators at participating sites) will be informed via email. If changes are made to the study processes, participants consent will be obtained again, if necessary.

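### The stated analysis names centre as its only covariate and does not use the pre-surgery CMR and echocardiography values when comparing the continuous 6-month imaging outcomes, which may lose precision

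*Protocol article*

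**What the plan says.** All references are to the protocol article.

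- **Statistical analysis** assigns a model to each type of outcome. Quantitative secondary outcomes go to "linear regression (quantitative outcomes), survival methods (time-to-event outcomes"). Repeated measures go to mixed models. One covariate rule covers everything: "Analyses will be adjusted for the centre (stratification factor").
- **Trial outcomes** defines the CMR outcome at 6 months, "defined as presence and degree of pulmonary regurgitation, end-diastolic volume and right ventricular ejection fraction". The echocardiography outcome, also at 6 months, is "presence and degree of pulmonary regurgitation and residual valve stenosis, measured as peak velocity through the valve". Neither is defined as a change from baseline.
- **Data collection, Table 1** has a row for "Cardiovascular magnetic resonance imaging" ticked before surgery and at 6 months. The echocardiography row is ticked at the same two times.
- **Changes to the protocol since REC approval** explains how the baseline imaging came in: "Shortly after opening to recruitment, we made one major change to the protocol", namely "to extend the baseline data collection to include the pre-surgery echocardiographic and CMR results".
- **Risk of bias** promises a detailed analysis plan before database closure and before the groups are compared.

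**The concern.** The trial amended its protocol to collect pre-surgery imaging, then states an analysis of the 6-month imaging that does not mention it. A patient's pre-operative ventricular volume and ejection fraction are the obvious candidates to predict the same quantities six months later. If they do, a comparison adjusted for centre alone leaves that predictable between-patient variation in the residual, and any chance baseline imbalance adds to the error of the estimate.

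The design offers no other protection. Randomisation is stratified by centre only, ages run from 12 to 80, and the target is 30 per group. Results are to be reported as effect sizes with 95% confidence intervals, and the trial is meant to inform larger ones, so interval width is a large part of what these outcomes deliver.

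**Working it through.** **1. The plan's own figure.** The article gives 60 participants (30 per group), 80% power, two-sided 5%, and an effect of −0.73 on the log scale. No SD is stated; I take SD = 1, so that 0.73 is a standardised effect.

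- n per group = 2 × (1.96 + 0.8416)² / 0.73² = 2 × 7.849 / 0.5329 = 29.5, rounded up to 30, total 60.
- Power with 30 per group is 80.7% by the normal formula and 79.4% by the noncentral t.

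The figure reproduces. It concerns 24-hour chest drain volume and is unaffected by this point. I use it only for the number of participants.

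**2. Which model the imaging outcomes receive.** End-diastolic volume, ejection fraction and peak velocity are quantitative and defined at one time point, so as written they fall under linear regression with centre. Quality of life, defined at 6 weeks and 6 months, is the outcome that fits the mixed-model sentence most naturally.

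**3. Effect of adding the baseline value.** For a continuous outcome in a linear model, adding the pre-surgery value multiplies the variance of the treatment effect by about 1 − r². Interval width is multiplied by √(1 − r²), and the equivalent sample size is 60 / (1 − r²). With 30 per group and no baseline term, in units of the outcome SD:

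- 95% CI half-width = 1.96 × √(2/30) = 0.51
- difference detectable at 80% power = 2.8016 × √(2/30) = 0.72

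The article does not give r, so every r below is an assumption. The table also assumes 60 complete pairs.

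| Assumed r | Variance × | CI width × | CI half-width (SD) | Equivalent N | Detectable difference (SD) | Power for 0.5 SD |
|---|---|---|---|---|---|---|
| 0 | 1.00 | 1.00 | 0.51 | 60 | 0.72 | 48% |
| 0.2 | 0.96 | 0.98 | 0.50 | 62.5 | 0.71 | 49% |
| 0.3 | 0.91 | 0.95 | 0.48 | 66 | 0.69 | 51% |
| 0.5 | 0.75 | 0.87 | 0.44 | 80 | 0.63 | 59% |
| 0.7 | 0.51 | 0.71 | 0.36 | 118 | 0.52 | 76% |

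Put the other way, the stated analysis would give intervals wider than needed by 5% at r = 0.3 (1/0.954), 15% at r = 0.5 (1/0.866) and 40% at r = 0.7 (1/0.714).

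**4. Cost of the extra term.** One slope is estimated. With 60 participants and terms for intercept, arm and centre, residual degrees of freedom fall from 57 to 56, a cost of roughly 1/56 = 1.8% in variance. The gain (r² = 4% at r = 0.2, 1% at r = 0.1) therefore covers the cost from about r = 0.13 upwards. Below that, little is lost.

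**5. Where the formula applies.** It suits end-diastolic volume, ejection fraction and peak velocity. It does not carry over directly to presence or grade of regurgitation. For peak velocity r may be low, because the baseline describes the valve being replaced and the 6-month value describes the new one.

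**The case against.** The strongest reply is that nothing in the article is false. Adjusting for the stratification factor is correct, the sentence does not say that centre is the only covariate, and covariates for individual secondary outcomes are commonly settled in the analysis plan that the article promises. The mixed-model sentence could also be read to cover imaging measured twice, and such a model would use the pre-surgery value. This stands to the extent that a reader who infers that the baseline imaging is deliberately discarded goes further than the text. The amendment suggests some intention to use it.

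It does not dispose of the point. The article does not defer the covariates; it states a rule for all analyses and names one covariate. The imaging outcomes are defined at 6 months only, which makes the mixed-model reading the less natural one. Adding a measurement that is already scheduled is a better method than the one stated, not merely missing detail.

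Four further objections hold and limit the claim:

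- No correlation is given, so a reader should not take an equivalent of 80 or 118 participants as an established loss.
- The gain should not be extended to every imaging outcome. For binary regurgitation analysed by logistic regression, adding a baseline term also changes the odds ratio being estimated.
- Because the amendment followed opening, some early baselines may be missing. Recruitment opened in April 2016 and the first patient was recruited in July 2016, so few may be affected, but the amendment date is not given.
- A reader might infer that the 6-month comparison is biased. Under randomisation it is not; the possible cost is precision, in secondary outcomes only.

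**Conclusion.** The point holds in a limited form. The stated analysis names centre alone and makes no described use of the pre-surgery imaging in the 6-month comparison. The consequence is a possible loss of precision for the continuous secondary imaging outcomes, chiefly end-diastolic volume and right ventricular ejection fraction. It is modest if r is about 0.3, material at 0.5 or above, and negligible below about 0.2.

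These sizes rest on assumed correlations, 30 per group with 6-month imaging, and a baseline value for nearly everyone. The primary analysis and the sample size are unaffected. This is an inexpensive improvement worth making, not an error that threatens the trial's main conclusion.

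**What to change.** Add to the Statistical analysis section, and carry into the analysis plan, a sentence such as:

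> Continuous 6-month imaging outcomes (end-diastolic volume, right ventricular ejection fraction and peak velocity) will be analysed by linear regression adjusted for centre and for the pre-surgery value of the same measure. A missing pre-surgery value will be replaced by a simple single imputation, such as the overall mean, made without regard to treatment arm, so that no participant is excluded for lack of a baseline.

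Baseline adjustment of binary or graded regurgitation is not required. The change should be fixed before any between-group comparison, which fits the timing the article already sets for its analysis plan.

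The cost is one sentence and one degree of freedom per model. No new measurement is needed, since Table 1 already schedules the baseline imaging. Where baselines are imputed, the gain shrinks with the proportion missing.
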